### Criteria for discontinuing or modifying allocated interventions {11b}

Patients may withdraw from the trial at any time for any reason. The AmT-P mixture was demonstrated as safe and tolerable at the same dosage and length in malnourished older adults [20]. We do not anticipate that severe harm to require early product discontinuation or medical intervention. However, participants will be withdrawn by the team involved in the trial if they experience any new-onset, moderate, or severe adverse events from the intervention. The trial will be terminated if > 20% of all participants exhibit adverse events of moderate or great severity which are new from baseline or progressively worsening.

No intervention dose modifications or administration frequency changes are allowed. Participants will be considered non-adherent and withdrawn from the trial if deviations from the dosing standard are reported to the study team.

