### Strategies to improve adherence to interventions {11c}

Adherence will be monitored daily throughout the trial, as the sachets of the placebo and the EAA supplementation will be administered by the team nurse and taken by the participants in front of them. Participants will be considered adherent by taking > 80% of expected doses throughout their participation in the trial. The study product will be stored in a locked cabinet in a locked room for future quality assessment.

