### Outcomes {12}

#### Primary outcome

Change of LBM with weight regain in patients with AN. The assessment of body composition will be performed at baseline (T0), at the end of the 13 weeks of treatment (T1), and at 24 weeks follow-up (T2) with the dual-energy X-ray absorptiometry (DXA) (Prodigy Primo Lunar, A223040501, General Electric Company, Madison. WI 53,707–7550, USA-EnCORE TM 2009 (v13.31) software). The DXA has been used in previous studies assessing the changes of LBM in patients with AN [27]. The Bioelectrical Impedance (BIA) (Tanita HealthWare® Native Software, Tokyo, Japan) will be used simultaneously to improve body composition measurement accuracy. Indeed, we will measure total body proteins with the method suggested by [28], which associates the DXA with the BIA data, which has good accuracy in evaluating total body water in patients with AN [29].

This primary outcome will be of extreme clinical importance as LBM deficit and abnormalities beyond total body skeletal muscle mass are associated with several severe medical repercussions in other populations, such as low bone mineral density [30], reduction in physical fitness (i.e., strength, metabolic function, and athletic performance) [31], more extended hospitalization [32], and high rates of mortality [33].

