### Sample size {14}

Since this is an efficacy study, the primary data evaluation will be the analysis of completers. The primary outcome of interest is the percentage increase in the patient’s LBM with weight recovery at the end of the intensive treatment. The sample size was determined based on the difference between the intervention group and the control group on the change in LBM between baseline and end of treatment. We hypothesized, referring to the data of our previous study [27], that the control group could have an 8.8% increase in LBM, while the intervention group could have a further 2% increase in LBM [48, 49] to reach a variation of LBM of 10.8%. The standard deviation assumed for the sample size calculation is 3.2%.

Based on these premises, will be necessary to have a group of completers of 80 patients at the end of the treatment (i.e., 40 patients per treatment condition). To calculate the initial sample needed to generate 80 patients at the end of treatment, we considered the intervention interruption rate (set at 15%). This calculation results from an initial sample of 92 patients (46 per treatment condition).

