### Plans to promote participant retention and complete follow-up {18b}

A maximum effort will be made to engage participants in as many assessments as possible and achieve a high adherence rate in the study. Appointments for the follow-up assessments will be offered at times that best suit the participants. Patients will be provided breaks during examinations, and the assessments can be split into several shorter sessions if required. The research team will electronically monitor participants’ adherence to the assessment schedules, using the treatment progress evaluation form. Retention rates will be continuously monitored by the principal investigator ([name]) during the entire course of the study.

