## Statistical methods

### Statistical methods for primary and secondary outcomes {20a}

At the end of the treatment, the LBM of the patient will be assessed, the blood chemistry and instrumental tests will be evaluated, and the scores of each questionnaire used will be calculated, assessing the effects of the treatment on the scores of each scale.

The univariate analysis (*t*-test for independent samples) will allow us to evaluate the differences at the end of treatment (T1) in the percentage of LBM between the intervention group and the control group. In addition, with mixed linear models, it will be possible to evaluate the difference between the two treatment arms in the primary and secondary outcomes at the end of therapy. Mixed linear models will be able to incorporate all available data collected in the study and effectively treat missing data commonly present in longitudinal studies. Models will be compared using maximum likelihood estimation rather than limited maximum likelihood estimation, as the focus is on the whole model, including fixed and random effects. The main clinical features (i.e., BMI, ED psychopathology, and general psychopathology) will be included in the models as potential predictors of the trajectories of change.

The analyses will also be controlled for physical activity and its variation between baseline and end of hospitalization (measured with the Actiheart system and IPAQ).

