### Methods in analysis to handle protocol non-adherence and any statistical methods to handle missing data {20c}

We will test superiority using two analysis sets; the intention-to-treat set, considering all patients as randomized regardless of whether they received the randomized treatment, and the “per protocol” analysis set. Criteria for determining the “per protocol” group assignment will be established by Data Manager before the trial begins.

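### Dosing deviations lead to withdrawal from the trial and not just from the product, so the intention-to-treat analysis may have to impute week-13 lean mass that could have been measured

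*Protocol article*

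**What the plan says.** All references are to the protocol article.

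- Section {11b}, on dosing: "Participants will be considered non-adherent and withdrawn from the trial if deviations from the dosing standard are reported to the study team". The sentence before it forbids changes of dose or administration frequency.
- Section {11b}, on harms: "participants will be withdrawn by the team involved in the trial if they experience any new-onset, moderate, or severe adverse events from the intervention". It does not say whether this means leaving the product or the trial. The same section speaks of early discontinuation of the product as a thing of its own.
- Section {11c}: nurses give the sachets and watch them being taken. "Participants will be considered adherent by taking > 80% of expected doses throughout their participation in the trial".
- Primary outcome, section {12}: DXA is done at baseline (T0), "at the end of the 13 weeks of treatment (T1), and at 24 weeks follow-up (T2"). No scan falls between T0 and T1.
- Section {14}: the primary data evaluation is of completers. The calculation uses 8.8% against 10.8% gain in lean body mass, SD 3.2%, 40 completers per arm, and a 15% interruption rate leading to 92 randomised.
- Section {18b}: "A maximum effort will be made to engage participants in as many assessments as possible". Withdrawn patients are not mentioned. The dropout form in section {18a} records the date and the patient's reasons.
- Section {20a}: "Mixed linear models will be able to incorporate all available data collected in the study".
- Section {20c}: superiority is tested in a per-protocol set and in an intention-to-treat set, the latter "considering all patients as randomized regardless of whether they received the randomized treatment". Dropouts enter by multiple imputation (15 datasets) from models built on participants with complete data. A sensitivity analysis for missing data is also planned.

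**The concern.** An analysis of all patients as randomised, whatever they took, needs outcomes from people who stopped taking the product. The rule in {11b} removes such people from the trial. Unless they are scanned anyway, the trial's own rule creates the missing values, and does so because of events after randomisation.

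At stake is what the intention-to-treat estimate means. For these patients it would rest on an imputation model and not on data, and no later analysis plan can recover scans that were never taken. There is also a lesser, indirect effect on the completer evaluation: the same rule helps decide, from post-randomisation events, who counts as a completer.

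**Working it through.** **1. Following a withdrawn patient through the text.** A patient withdrawn before week 13 has a T0 scan and no later one, because T1 is the first post-baseline DXA. The mixed models in {20a} then hold only that patient's baseline value, which says nothing about change. The patient can enter the intention-to-treat set only through the imputation in {20c}. That section speaks of different models for different kinds of patient, but if nobody off product is scanned there are few or no off-product T1 values to fit such models to.

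**2. Could the value have been obtained?** Often, yes. The intensive treatment lasts 13 weeks, seven days a week, and section {15} says that leaving the study does not affect later treatment. A patient stopped for a dosing deviation could well still be attending at T1.

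**3. The plan's own figure.** Significance level and power are not given with the sample size; I assume two-sided 5% and 80%. Then n per arm = 2 × (1.960 + 0.842)² × 3.2² / 2² = 40.2, rounded up to 41, against 40 stated. A t-test with 40 per arm has power 78.8%. The 92 is 80 × 1.15. The planning figures are therefore usable for illustration.

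**4. Illustration of size.** Two quantities are assumed, since the article gives neither:

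- w: the share of each arm withdrawn under {11b} before T1;
- k: the share of the benefit those patients would still show at T1.

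With a 2-point difference among on-product patients:

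- as-randomised difference = 2 × (1 − w(1 − k));
- imputing within arm from on-product patients gives about 2.0, an excess of 2w(1 − k);
- imputing without regard to arm gives 2 × (1 − w), a shortfall of 2wk.

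| w (of 92) | As randomised, k = 0 | As randomised, k = 0.5 | Within-arm excess, k = 0 / 0.5 | Arm-blind result |
|---|---|---|---|---|
| 5% (4.6) | 1.90 | 1.95 | 0.10 / 0.05 | 1.90 |
| 10% (9.2) | 1.80 | 1.90 | 0.20 / 0.10 | 1.80 |
| 15% (13.8) | 1.70 | 1.85 | 0.30 / 0.15 | 1.70 |

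The within-arm excess is zero if w = 0 or k = 1. The 15% row is an extreme: it would make every interruption allowed for in {14} a withdrawal under {11b}, leaving none voluntary.

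A simulation (46 per arm, 7 per arm withdrawn, 15 imputations, 3,000 runs) agrees. For k = 0 it gave 1.69 with observed values, 2.00 imputed within arm and 1.69 arm-blind. For k = 0.5 it gave 1.87, 2.03 and 1.72.

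**5. Scale.** The standard error of the difference at 40 per arm is 3.2 × √(2/40) = 0.72 points. The within-arm excess is thus about 0.07 to 0.14 standard errors at w = 5%, and at most 0.30/0.72 = 0.42 in the extreme row.

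**6. Power after the change.** At w = 15% with all 46 per arm scanned, t-test power is 71.2% (k = 0, difference 1.70) or 78.3% (k = 0.5, difference 1.85), against 78.8% for 2 points at 40 per arm. These are best cases, because some patients who leave treatment would still not be scanned.

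**The case against.** The strongest reply has four parts.

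- **The primary evaluation is of completers.** A reader might infer that the trial's primary analysis is undermined. The article does not support that: patients withdrawn under {11b} are outside a completer analysis by design. What remains is the direct harm to the intention-to-treat test that {20c} also commits to, and the influence of {11b} on who completes.
- **Loss of the scan is partly inferred from silence.** No sentence cancels T1 for withdrawn patients. The schedule table and the flow figure, where this might appear, are not shown, and an article condenses a fuller protocol. It would therefore go too far to say that these scans will certainly be missing. But withdrawal from the trial is a stated rule, not an omitted detail, and the general promise in {18b} does not override it.
- **Missing data are to be examined.** Section {20c} plans a sensitivity analysis and reporting of withdrawal reasons by arm. That tests the reliance on assumptions; it does not replace observed values.
- **Few patients may be affected.** Dosing is nurse-observed and {11b} expects no severe harm. This stands, and it limits the size of the point.

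A further tempting reading is that {11b} contradicts {11c}, so that one missed sachet removes a patient whom {11c} calls adherent. Doses number 2 × 7 × 13 = 182; more than 80% means at least 146 taken, so up to 36 may be missed. But the sentence before the dosing rule concerns changes of dose and frequency. If the rule covers only those, there is no conflict, so no contradiction is established.

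**Conclusion.** The point holds in a limited form. The wording of {11b}, followed literally, gives up T1 lean-mass values that the intention-to-treat analysis in {20c} needs and that could often be measured. The direct harm is to that analysis, not to the completer evaluation named as primary.

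The size cannot be derived from the article and is probably small. The illustrative excess of 0.05 to 0.30 points on a 2-point difference rests on assumed values of w and k and on imputation within arm from on-product patients. A reader might infer a known bias in favour of the product. The article does not support that, because the direction depends on an imputation model that is not fixed in detail: arm-blind imputation would err the other way whenever some benefit persists. The conclusion also assumes that the table and figure not shown do not provide for scanning withdrawn patients.

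**What to change.** - In {11b}, replace withdrawal from the trial with discontinuation of the product for dosing deviations, and say the same for adverse events. Patients with adverse events still stop the product, so their protection is unchanged.
- State that T1 and T2 DXA will be sought for every randomised participant who has not withdrawn consent.
- In {20c}, use these observed values in the intention-to-treat analysis and impute only where T1 was not obtained.
- Use the adherence threshold in {11c} only to define the per-protocol set. For clarity, say whether the dosing rule in {11b} covers missed sachets or only altered doses and schedules.

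The cost is a small amendment and a few scans of patients off product, some of whom may have left the programme. The observed intention-to-treat difference may be below 2 points, and no power gain should be expected. What improves is that the as-randomised comparison rests on data.

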### Strategies to improve adherence to interventions {11c}

Adherence will be monitored daily throughout the trial, as the sachets of the placebo and the EAA supplementation will be administered by the team nurse and taken by the participants in front of them. Participants will be considered adherent by taking > 80% of expected doses throughout their participation in the trial. The study product will be stored in a locked cabinet in a locked room for future quality assessment.

### Relevant concomitant care permitted or prohibited during the trial {11d}

Participants will be allowed antidepressants, benzodiazepines, mood stabilizers, and atypical antipsychotics to manage psychiatric comorbidly and multivitamins during the treatment. Any protein and AA supplements and anabolic drugs are prohibited during the trial.

### Provisions for post-trial care {30}

There is no anticipated harm and compensation for trial participation.

### Outcomes {12}

#### Primary outcome

Change of LBM with weight regain in patients with AN. The assessment of body composition will be performed at baseline (T0), at the end of the 13 weeks of treatment (T1), and at 24 weeks follow-up (T2) with the dual-energy X-ray absorptiometry (DXA) (Prodigy Primo Lunar, A223040501, General Electric Company, Madison. WI 53,707–7550, USA-EnCORE TM 2009 (v13.31) software). The DXA has been used in previous studies assessing the changes of LBM in patients with AN [27]. The Bioelectrical Impedance (BIA) (Tanita HealthWare® Native Software, Tokyo, Japan) will be used simultaneously to improve body composition measurement accuracy. Indeed, we will measure total body proteins with the method suggested by [28], which associates the DXA with the BIA data, which has good accuracy in evaluating total body water in patients with AN [29].

This primary outcome will be of extreme clinical importance as LBM deficit and abnormalities beyond total body skeletal muscle mass are associated with several severe medical repercussions in other populations, such as low bone mineral density [30], reduction in physical fitness (i.e., strength, metabolic function, and athletic performance) [31], more extended hospitalization [32], and high rates of mortality [33].

#### Secondary outcomes

The secondary outcomes of the study include the changes between T0 and T1 of the following physical and psychological features:Physical fitness measured with the Eurofit Physical Fitness Test Battery (EPFTB) [34].Physical activity measured with the Actiheart system, CamNtech Ltd., Cambridge, UKWeight regain measured with the Seca Digital Wheelchair Scale Model 664 (Seca, Hamburg, Germany).ED psychopathology assessed with the Eating Examination (EDE) Interview [35, 36], the EDE Questionnaire (EDE-Q) [37, 38], and the Eating Problem Check List (EPCL) [39].General psychopathology assessed with the Brief Symptom Inventory (BSI) [40, 41].Clinical impairment secondary to EDs assessed with the Clinical Impairment Assessment (CIA) [42, 43] and the Starvation Symptom Inventory (SSI) [44].

The measurement of the above physical features was chosen as secondary outcomes because they represent potential mediators of the efficacy of the EEA mixture in improving the LBM. At the same time, improving the eating disorder and general psychopathology and reducing the clinical impairment is the primary goal of treating AN.

Other outcomes of the study include the changes between T0 and T1 of the following:Plasma metabolome and miRNAome [45].Mitochondrial mass and bioenergetics parameters (mtDNA, enzymatic functions of respiratory chain complexes), transcriptome (RNA-seq), methylome.Fecal metagenome. [46, 47].Urine metabolome.

The exams were chosen as secondary outcomes to improve our understanding of the underlying mechanisms of action of the AmT-P mixture in changing the LBM.

### Participant timeline {13}

Patients will be screened with an in-person clinical screening visit by a study physician on the day of admission to the unit (T0) to determine initial eligibility. If the candidate is eligible, they are evaluated on the same day in randomization visits. All additional visits of the physician will occur biweekly for the duration of the intervention and follow the procedure flow according to Fig. 1 and Table 3.

**Table 3 Tab3:**
[figure not shown]
Study schedule of enrolment, interventions, and assessments

*DXA* Dual-energy X-ray absorptiometry, *BIA* Bioelectrical impedance analysis, *AS* Actiheart System, *EPFTB* Eurofit Physical Fitness Test Battery, *EDE.17* Eating Disorder Examination Interview, *EDE-Q* Eating Disorder Questionnaire, *EPCL* Eating Problem Check List, *CIA* Clinical Impairment Assessment, *SSI* Starvation Symptom Inventory, *BSI* Brief Symptom Inventory, *IPAQ* International Physical Activity Questionnaire

**Fig. 1 Fig1:**
[figure not shown]
Illustration of the participant flow through the study. CBT-E = enhanced cognitive behavior therapy

### Sample size {14}

Since this is an efficacy study, the primary data evaluation will be the analysis of completers. The primary outcome of interest is the percentage increase in the patient’s LBM with weight recovery at the end of the intensive treatment. The sample size was determined based on the difference between the intervention group and the control group on the change in LBM between baseline and end of treatment. We hypothesized, referring to the data of our previous study [27], that the control group could have an 8.8% increase in LBM, while the intervention group could have a further 2% increase in LBM [48, 49] to reach a variation of LBM of 10.8%. The standard deviation assumed for the sample size calculation is 3.2%.

Based on these premises, will be necessary to have a group of completers of 80 patients at the end of the treatment (i.e., 40 patients per treatment condition). To calculate the initial sample needed to generate 80 patients at the end of treatment, we considered the intervention interruption rate (set at 15%). This calculation results from an initial sample of 92 patients (46 per treatment condition).

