#### Imputation procedure for missing data

We will report reasons for withdrawal for each randomization group and compare the reasons qualitatively. Any missing data’s effect on results will be assessed via sensitivity analysis of augmented data sets. Dropouts will be included in the analysis by modern imputation methods for missing data.

The main feature of the approach is creating a set of clinically reasonable imputations for the respective outcome for each dropout. This will be accomplished using a set of repeated imputations created by predictive models based on the majority of participants with complete data. The imputation models will reflect uncertainty in the modeling process and inherent variability in patient outcomes, as reflected in the complete data.

After the imputations are completed, all of the data (complete and imputed) will be combined, and the analysis performed for each imputed-and-completed dataset. Rubin’s multiple (i.e., repeated) imputation method will be used to estimate the treatment effect. We propose to use 15 datasets (an odd number to allow use of one of the datasets to represent the median analytic result).

These methods are preferable to simple mean imputation, or simple “best–worst” or “worst-worst” imputation, because the categorization of patients into clinically meaningful subgroups, and the imputation of their missing data by appropriately different models, accords well with best clinical judgment concerning the likely outcomes of the dropouts, and therefore will enhance the trial’s results.

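### The only analysis called primary is restricted to completers, conflicts with the as-randomised analyses named elsewhere, and is open to selection bias of unknown size and direction

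*Protocol article*

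**What the plan says.** All references are to the Protocol article.

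- Sample size {14} fixes the population of the main analysis: "Since this is an efficacy study, the primary data evaluation will be the analysis of completers". The target of 80 (40 per arm) counts completers. This is the only place where a population is called primary.
- Section {20c}, on non-adherence and missing data, reads: "We will test superiority using two analysis sets; the intention-to-treat set, considering all patients as randomized regardless of whether they received the randomized treatment". The second set is per protocol. Completers are not mentioned, and neither set is placed above the other.
- The imputation subsection of {20c} says: "Dropouts will be included in the analysis by modern imputation methods for missing data". It then uses Rubin's method with 15 datasets to estimate the treatment effect. The same subsection also says: "Any missing data’s effect on results will be assessed via sensitivity analysis of augmented data sets".
- Statistical methods {20a} gives an independent-samples t-test at T1 and, additionally, mixed models for the primary and secondary outcomes: "Mixed linear models will be able to incorporate all available data collected in the study".
- Criteria for discontinuing {11b} says that "participants will be withdrawn by the team involved in the trial if they experience any new-onset, moderate, or severe adverse events from the intervention". It also withdraws participants reported to have departed from the dosing standard.

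**The concern.** Two problems meet here.

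First, the document does not say which result decides the trial. A completer analysis, an as-randomised analysis with imputed dropouts and a per-protocol analysis answer different questions and can disagree. Only the first is called primary, yet superiority is to be tested in the other two.

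Second, the set that is called primary is formed after randomisation. Whether a participant completes depends partly on tolerability and on withdrawal decisions by the team, and either may differ by arm. Randomisation balances the 92 people who enter, not the subset who finish. Describing the trial as an efficacy study does not restore that balance, and Trial design {8} calls it a superiority trial. If one arm loses more of the participants who were gaining little lean body mass (LBM), its completer mean rises for reasons unrelated to the supplement.

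**Working it through.** **The plan's own figure.** Inputs from {14}: difference 10.8 − 8.8 = 2 points, SD 3.2, 40 completers per arm. Alpha and power are not stated, so two-sided 5% and 80% are assumed.

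- n per arm = 2 × (1.96 + 0.84)² × 3.2² / 2² ≈ 40.2, rounded up to 41, against the stated 40.
- Power at 40 per arm: SE = 3.2 × √(2/40) = 0.716; 2/0.716 = 2.795; Φ(2.795 − 1.96) = 79.8%.
- One-sided 5% at 80% power would need only 32 per arm and does not match.

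The completer target therefore reproduces to within one patient per arm. The step from 80 to 92 is 80 × 1.15; that inflation is a separate matter and is not used below.

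**Size of the selection bias.** Suppose there is no true effect and dropouts in both arms gain g points less LBM than completers. If d is an arm's dropout rate, the mean over everyone randomised is μ = c − d × g, so the completer mean is c = μ + d × g. The completer contrast is then biased by

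bias = (d on AmT-P − d on placebo) × g.

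The protocol gives only an overall 15%. The arm-specific rates and g below are assumptions. With 20% and 10% dropout, 46 × 0.80 = 36.8 and 46 × 0.90 = 41.4 complete, so SE = 3.2 × √(1/36.8 + 1/41.4) = 0.725.

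| Dropout, AmT-P vs placebo | g (points) | Bias (points) | Share of the 2-point target | Two-sided type I error |
|---|---|---|---|---|
| 15% vs 15% | any | 0 | 0% | 5.0% |
| 20% vs 10% | 1.6 (0.5 SD) | +0.16 | 8% | 5.6% |
| 20% vs 10% | 3.2 (1 SD) | +0.32 | 16% | 7.3% |
| 20% vs 10% | 6.4 (2 SD) | +0.64 | 32% | 14.3% |
| 10% vs 20% | 1.6 to 6.4 | −0.16 to −0.64 | 8% to 32%, against AmT-P | as above |

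Example for g = 3.2: 0.32/0.725 = 0.441, and the rejection probability is [1 − Φ(1.96 − 0.441)] + Φ(−1.96 − 0.441) = 7.3%. The last value of g is extreme: with completers at 8.8%, dropouts would gain 8.8 − 6.4 = 2.4%.

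**Does imputation alone cure it?** The imputation subsection of {20c} builds its models from participants with complete data. If dropouts do worse than those models predict, imputing each arm's dropouts around that arm's completer mean leaves the contrast at c(AmT-P) − c(placebo), and the bias stays. A mixed model has the same limit for anyone whose only LBM value is the baseline scan. Correction has to come from information on the dropouts themselves: weights during treatment, or the T1 scan.

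**Power of an as-randomised analysis of 92.** SE = 3.2 × √(2/46) = 0.667. With 15% dropout, the expected difference is 2 × [1 − 0.15 × (1 − f)], where f is the share of the effect that dropouts keep.

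| f | Difference (points) | Power |
|---|---|---|
| 1 | 2.00 | 85% |
| 0.5 | 1.85 | 79% |
| 0 | 1.70 | 72% |

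These figures treat every outcome as observed; imputation would lower them somewhat.

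**The case against.** The strongest reply is that the text is less disordered than it looks. Section {14} does name a primary set. Section {20a} introduces the mixed models as an addition to the t-test, {20b} labels the baseline-adjusted analysis secondary, and the imputation subsection partly describes itself as sensitivity work. On that reading completers are primary and the rest is supportive. What defeats it is {20c}, which assigns the superiority test itself to two other sets, and the statement that dropouts enter the estimate of the treatment effect. The hierarchy may be intended, but it is not written down. Even if it were, the primary set would still be chosen by events after randomisation.

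A second reply stands in large part: differential dropout is less likely here than in many trials. The trial is double-blind, the placebo is isocaloric, intake is observed by a nurse, and both arms receive the same intensive programme. This lowers the probability of bias but does not remove it, because {11b} ties withdrawal to adverse events attributed to the intervention.

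A reader might also infer that several analyses mean several chances to claim success, and put a figure on the inflated type I error. The document does not support one. It would need a per-protocol exclusion rate and a baseline-to-outcome correlation, neither of which is given, and it should not count an analysis already labelled secondary. That the per-protocol criteria are not printed is no fault in itself: "Criteria for determining the “per protocol” group assignment will be established by Data Manager before the trial begins".

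**Conclusion.** The contradiction is certain on the wording. Section {14} makes completers primary, {20c} tests superiority in two unranked other sets and includes dropouts by imputation, {20a} offers two models, and no section says which decides. It is also certain that completion is determined after randomisation.

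The size of the harm is not known. A reader might infer that the completer result will flatter AmT-P; the document does not show that. The bias is zero when the rate and type of dropout are the same in both arms, and it runs against AmT-P if placebo loses more poor responders. The range of 0.16 to 0.64 points, with type I error of about 5.6% to 14%, rests wholly on an assumed 20% against 10% dropout and an assumed shortfall of 0.5 to 2 SD.

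The point still needs correcting, because as written the one analysis labelled primary in a superiority trial gives up the protection of randomisation.

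**What to change.** 1. In {14}, delete the sentence that makes completers the primary evaluation.
2. In {20c}, name one primary analysis with one model: all randomised participants, analysed as allocated, using either the multiple imputation or the mixed model already planned. State in {20a} that this model decides the primary outcome.
3. Include baseline LBM and the body weights recorded during treatment as auxiliary variables. Confirm how often weights are captured: Table 2 lists weekly weighing as a treatment procedure, but the treatment progress evaluation form states no frequency.
4. Seek the planned T1 DXA in participants who stop the supplement or are withdrawn, where they agree. This makes the as-randomised result observed rather than modelled.
5. Label the completer and per-protocol analyses supportive, with no superiority claim from either alone.
6. Restate the power for 92 analysed as randomised, giving the assumed share of effect kept by dropouts (about 85%, 79% or 72% for all, half or none, before any loss from imputation).

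The cost is wording in {14}, {20a} and {20c}, some extra T1 scans and a little more analysis. The as-randomised estimate may be less favourable than the completer estimate, and power may fall below 80% if dropouts keep half the effect or less. No additional enrolment is proposed.
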